### Statistical analysis

After the database is audited and locked, the statistical analysis will be conducted by a statistician independent of the sponsor and the CRO. The statistical plan described in the study protocol includes details about handling missing data, assessing comparability of randomized groups, and evaluating the pooled data collected at the various centers.

The data from the study will only be analyzed once at the end of the study, and no formal statistical stopping rules allow for the early termination of this study.

The analysis groups include the (1) intent-to-treat (ITT) population, defined as all patients who were randomized with a study group defined by the randomization; (2) modified intent-to-treat (mITT) population, defined as the complete control group and a subset of the ITT therapy group with successful cannulation of the left subclavian vein; and (3) per protocol (PP) population, i.e., a subset of the mITT population defined as those patients who completed at least 75% of the protocol-required stimulations in at least one phrenic nerve. The sidedness of the phrenic nerve stimulation can change from left to right or can occur in both phrenic nerves.

Descriptive statistics for continuous variables will include the number of observations, mean, standard deviation, minimum, median, and maximum. Descriptive statistics for categorical variables will include the number and percent in each category out of the total number of observed responses. The *p* values will be considered statistically significant if the two-sided *p* value is ≤0.05 unless otherwise specified. When the arithmetic mean is found not to be an appropriate measure of central tendency, alternative statistics will be considered (e.g., median, interquartile range). When the distribution of a variable does not support the use of parametric statistics, nonparametric approaches or data transformations may be implemented. If data transformations are used, they will be specified in the final clinical study report.

Regarding the primary efficacy endpoint (time to successful extubation without reintubation in the next 48 h), the null hypothesis states the cumulative incidence by day 30 for successful weaning is the same in patients randomized to treatment or control groups. The primary statistical analysis will be conducted on the mITT population and will model the time to the event of interest in the presence of competing events which include death and withdrawal of life support. In addition, cessation of weaning in the ICU with discharge from ICU to a specialized weaning facility will be evaluated. Patients who do not meet one of the endpoints by the end of their study follow-up will be censored at the time of study discontinuation or completion. The primary statistical model will utilize the cumulative incidence function. The event of interest, successful weaning, will be compared between randomized groups using Gray’s test. The probabilities will be summarized for successful weaning and each competing event for the duration of the study. The 95% confidence intervals will be provided for the probabilities at 30 days. In addition, descriptive statistics will be prepared by randomized group for the time to successful weaning in days.

All ITT patients will be included in the primary safety endpoint analysis. Fisher’s exact test will be used to compare the number of patients with an event or in a category of events out of the total number of patients randomized between groups as a tool to understand the adverse event profile associated with TTVDP compared to control.

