### Population size

The sample size needed to show a statistically significant difference between treatment depends on the proportion of patients successfully weaned and the proportion succumbing to a competing risk prior to successful weaning by day 30 (see the previous section “Outcomes”). Since TTVDP is a novel, first-of-its-kind therapy both in general and in the population of patients experiencing difficult weaning from MV, no estimates of the effect size or the competing events were available. Consequently, a sample of convenience was used to allow enrollment and randomization of up to 88 study patients (44 per arm).

Using a competing risks model with a log rank test (PASS 14, NCSS Statistical Software, LLC, Kaysville, UT, USA), this population size gives the study a 70% power to find a statistically significant difference in the event of a dramatically large treatment effect (i.e., approximately 50% of patients weaned with 34% experiencing one of the competing risks in the control group, vs. 80% weaned with 11% experiencing one of the competing risks in the TTVDP group).

As a result, the totality of evidence is expected to indicate a trend in favor of TTVDP (with an adverse event profile not significantly different between the groups) rather than to show definitive superiority.

Of note, Revision F of the protocol as described in this manuscript is being amended to account for a higher than expected number of withdrawals due to inability to insert the guidewire: the target size population will be brought from 88 to 110, with the possibility for sites to include two roll-in subjects for training purposes. Accordingly, the number of participating centers will be increased from 14 to 22.

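### The primary efficacy set removes TTVDP patients with failed cannulation but keeps every control, so it does not test the stated null and can be biased in either direction

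*Protocol article*

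**What the plan says.** All of this is in the article's Statistical analysis section unless stated otherwise.

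- **Primary set:** "The primary statistical analysis will be conducted on the mITT population".
- **mITT definition:** "the complete control group and a subset of the ITT therapy group with successful cannulation of the left subclavian vein".
- **ITT definition:** "defined as all patients who were randomized with a study group defined by the randomization". The only use of ITT that the article names is for safety: "All ITT patients will be included in the primary safety endpoint analysis".
- **Null hypothesis:** "the cumulative incidence by day 30 for successful weaning is the same in patients randomized to treatment or control groups". Weaning is to be "compared between randomized groups using Gray"'s test.
- **Censoring:** patients without an endpoint "will be censored at the time of study discontinuation or completion".
- **Cannulation failures (Population size):** the protocol is being amended because of "a higher than expected number of withdrawals due to inability to insert the guidewire", and the target rises from 88 to 110.

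**The concern.** Whether the left subclavian vein can be cannulated becomes known only after randomisation, and only in patients allocated to TTVDP. The mITT rule acts on that information in one arm. Nobody can identify the controls in whom insertion would also have failed, so they all remain. The two groups compared are then not the two groups that randomisation formed, and they are not the groups named in the null hypothesis.

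If patients who cannot be cannulated have a different chance of weaning from the rest, the primary p-value and the day-30 weaning probabilities can differ between arms with no device effect. The article's report of more insertion failures than expected shows that the rule will remove real patients. Eligibility criteria screens out only known anatomical barriers, and failures occurred all the same.

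A second point is linked to the first. Failed insertions are called withdrawals, and patients are censored when they discontinue the study. The article does not say whether weaning follow-up continues after a failed insertion, so it is unclear whether their primary outcome would be available for an analysis of all randomised patients.

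**Working it through.** **1. The plan's own power figure.** Inputs (Population size): 44 per arm; control 50% weaned and 34% with a competing event; TTVDP 80% and 11%; two-sided 0.05. With constant cause-specific hazards over 30 days, the weaning hazard is −ln(1 − F_w − F_c) × F_w/(F_w + F_c), where F_w and F_c are the day-30 proportions weaned and with a competing event.

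- Control: −ln(0.16) × 0.50/0.84 = 1.091
- TTVDP: −ln(0.09) × 0.80/0.91 = 2.117
- Hazard ratio: 2.117/1.091 = 1.94
- Weaning events: 44 × (0.50 + 0.80) = 57.2
- Power (Schoenfeld): Φ(√(57.2/4) × ln 1.94 − 1.96) = 0.71

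The stated 70% is reproduced, on the cause-specific log-rank scale. Gray's test, the planned primary test, has about 86% in the same scenario with no failures.

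**2. The failure rate.** None is given. Reading 88 to 110 as inflation for loss gives 1 − 88/110 = 20%, equivalently 11 of 55 in the TTVDP arm. If the aim is 88 analysable patients with every loss in one arm, it is 22/55 = 40%. The range used is 10% to 40%.

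**3. The apparent effect with no device effect.** Let f be the failure proportion and p the proportion of failures who wean, with 50% weaned overall. The TTVDP arm after exclusion shows (0.50 − f·p)/(1 − f), against 0.50 in control. For f = 0.20:

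- p = 0.30: 0.44/0.80 = 55%
- p = 0.20: 0.46/0.80 = 57.5%
- p = 0.10: 0.48/0.80 = 60%

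**4. Type I error of Gray's test.** Simulation with no device effect, 50% weaned and 34% competing events overall, and complete follow-up to day 30; nominal 5%, 44 per arm:

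| Failures | Weaned among failures | mITT, two-sided | of which favouring TTVDP |
|---|---|---|---|
| 10% | 30% | 5.9% | 4.4% |
| 10% | 20% | 6.1% | 4.9% |
| 20% | 50% (same prognosis) | 4.9% | 2.3% |
| 20% | 30% | 7.9% | 7.0% |
| 20% | 20% | 10.2% | 9.8% |
| 20% | 70% (better prognosis) | 6.9% | 0.9% (6.0% against) |
| 40% | 30% | 18.9% | 18.7% |
| 40% | 20% | 37.7% | 37.7% |

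At 20% failures of whom 10% wean, a separate run gave about 14%. At 55 per arm and 20% failures, the figures for 30%, 20% and 10% weaned are about 8%, 12% and 17%. ITT stayed between 4.4% and 5.5% in the tabulated scenarios.

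**5. Power cost of ITT.** Take the plan's scenario with 20% failures at control rates. The TTVDP arm as randomised has 0.8 × 80% + 0.2 × 50% = 74% weaned and 0.8 × 11% + 0.2 × 34% = 15.6% competing. The cause-specific hazard ratio falls to 1.71.

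| | n=88 | n=110 |
|---|---|---|
| Gray's test, ITT | about 67% | about 76% |
| Gray's test, mITT | about 83% | about 89% |
| Cause-specific log-rank, ITT | about 51% | about 60% |

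**The case against.** The mITT set is prespecified and disclosed, and it addresses a legitimate question: the effect in patients in whom the device can be placed. The sample is one of convenience, and Population size expects a trend rather than definitive superiority, so false-positive inflation matters less than in a confirmatory trial. Eligibility criteria also removes, from both arms, known anatomical barriers, a BMI of 40 or more, haemodynamic instability, sepsis and weaning failure from hypervolaemia. That weakens the routes by which cannulation difficulty could track prognosis.

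These points limit the size of the concern but do not remove it. A two-sided 0.05 test is still planned, and the set it runs on does not match its null hypothesis. An ITT sensitivity analysis in a document not shown would not change which result is primary.

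Three stronger readings are tempting, and the article does not support them:

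- *That the analysis favours the device.* It can, but the outcome of patients with failed cannulation is unknown. Equal prognosis gives no bias, and better prognosis reverses it.
- *That an ITT efficacy analysis would merely repeat mITT because failures are censored near day 0.* The article names no ITT efficacy analysis. Study setting follows trial patients to liberation or 30 days, and all study patients to day 30 for serious adverse events, admissions, discharges and mortality. Whether a withdrawal here is from treatment or from follow-up is ambiguous.
- *That ITT would keep about the 70% power stated.* The 67% and 76% are for Gray's test, whereas the 70% is reproduced on the cause-specific log-rank scale, where ITT gives about 51% and 60%.

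**Conclusion.** The concern holds. The primary efficacy analysis rests on a one-sided exclusion made after randomisation and conflicts with the null hypothesis stated in the same section. The direction and size of any bias cannot be fixed from the article; they depend on an assumed failure rate and an assumed prognosis of the failures. Over the ranges examined at 44 per arm, the two-sided type I error runs from the nominal 5% (equal prognosis), through about 6% (10% failures) and 7-14% (20% failures, poor prognosis), to about 19-38% (40% failures, 30% or 20% weaned). The status of failed insertions in weaning follow-up is a separate ambiguity that has to be settled for an ITT analysis to be informative.

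**What to change.** 1. Make ITT (all randomised patients, as randomised) the primary efficacy population, and mITT supportive.
2. State that failed guidewire insertion or cannulation is not in itself a study withdrawal. These patients are followed to day 30 for weaning and competing events and are not censored at the failed attempt.
3. If an effect in cannulable patients is wanted, a complier-average estimate (the ITT day-30 difference divided by the proportion cannulated) may be added as supportive only. It assumes that a failed attempt does not itself affect outcome, which may not hold given the catheterisation risks acknowledged under Risk-benefit balance.

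The cost is wording, in a protocol already being amended, and weaning follow-up for a group whose serious adverse events, discharges and mortality are already followed to day 30. The real downside is power. With 20% failures at control rates, moving from mITT to ITT loses about 16 points at n=88 (83 − 67) and 13 at n=110 (89 − 76) with Gray's test. The amended protocol should report this, name the test behind each power figure, and not set a Gray's-test figure beside the existing 70%.

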### Monitoring, auditing, and strategy to improve adherence to the protocol

Adverse events are reviewed by a medical monitor to determine whether the adverse event is serious and to identify the SAEs that are unanticipated. SAEs are further adjudicated by an independent Clinical Events Committee with respect to relationship to the device or procedure. Additionally, a Data and Safety Monitoring Board will periodically review the study data and may recommend early termination of the trial for safety concerns. A routine audit was conducted of the CRO at initiation of the study, and a second will be conducted before the completion.

Data management, monitoring, and auditing will be provided by an independent CRO. eCRFs will be reviewed by a clinical monitor appointed by the CRO who will determine acceptability with respect to data integrity, completeness, and accuracy. Queries will be generated for omissions, reasons for missing data, corrections, and clarifications. The monitors will perform source data verification and a review of informed consent processes and study procedures. In addition to the CRO, the study sponsor may conduct announced or unannounced monitoring visits or audits of the investigational sites.

Sponsor representatives are responsible for ongoing site support which involves any retraining should a pattern emerge regarding adherence to the protocol. Investigator meetings are held once a year, and routine newsletters are provided to the investigative sites. Mini pocket protocols have been provided to the sites as well as training tools on common procedures. Sponsor representatives also conduct reviews of patient cases with the site investigators to address any concerns. Through the monitoring process the sponsor is notified of any protocol deviations and evaluates the reason behind the deviation and decides if a change to the protocol is needed or if corrective action is needed to prevent these from reoccurring. Retraining is conducted by the sponsor if warranted as the sponsor representatives engage with each investigative site.

### Ethics, amendments, and dissemination

The RESCUE 2 study has been ethically approved by competent institutional bodies in the two participating countries. In France, a global authorization relevant for all study sites has been granted by the Comité de Protection des Personnes Sud-Est VI, Clermont-Ferrand, France (decision number dated November 9, 2017) and by the competent authority (Agence Nationale de Sécurité du Médicament et des produits de santé) on June 3,2017. In Germany, the study has been approved by the central Ethics Committee RWTH Aachen (August 14, 2017), which is relevant for each participating center, and the competent authority (Bundesinstitut fur Arzneimittel und Medizinprodukte (BfArM)) on September 1, 2017 .

The RESCUE 2 study is publicly registered at the ClinicalTrials.gov database (NCT03096639) and the European Database on Medical Devices (Eudamed CIV-17-06-020004).

After data review, resolution of all queries, and completion of the database audit trail according to the protocol data management plan, the database will be locked and the preplanned statistical analysis conducted. Results will be presented at national and international conferences and submitted to peer-reviewed journals. Post-publication press releases are possible.

### Substudies

Participating centers are allowed to conduct substudies, provided that (1) no interference with the primary protocol occurs; (2) approval by the local institutional review board is obtained; and (3) the steering committee and the sponsor accept the proposal according to its originality, feasibility, and importance. Currently, substudies with electrical impedance tomography, magnetic phrenic nerve stimulation, respiratory system mechanics and variables, and transpulmonary pressure measurements are under evaluation. Publication of substudies, in any form, will not occur until the results of the primary study have been published.

## Discussion

The RESCUE 2 study will be the first controlled study of temporary transvenous diaphragm pacing (TTVDP) in patients who are difficult to wean from MV, a highly relevant clinical challenge. It will be the first study to specifically address VIDD as the cause of weaning failure and to test the hypothesis that TTVDP can accelerate difficult weaning from MV. This hypothesis is supported by the likely pathophysiological role of ICU-acquired diaphragmatic dysfunction in difficult-to-wean patients and by the known capacity of diaphragm pacing to correct diaphragmatic disuse atrophy in long-term MV-dependent patients with quadriplegia.

### Position of the study in the landscape of weaning therapeutic trials

Accelerating weaning from MV has been a major preoccupation of ICU management in general for several decades, and it is a constant focus of intensivists regarding each of their mechanically ventilated patients [38]. Protocolizing the weaning process can reduce the duration of mechanical ventilation [39] with automated weaning as a possible further step [40]. In the particular context of difficult weaning, therapeutic approaches correcting ICU complications can be useful (e.g., correction of delirium [41], correction of anemia [42, 43], alleviation of anxiety [44]), as can be the reduction of the load imposed on the inspiratory muscles (augmentation of cough [45], reduction in work of breathing through optimization of posture [46], and inhalation of low viscosity gas mixtures [47]). Correcting weaning-induced cardiovascular compromise, a major pathophysiological determinant of weaning failure in specific patients, has also been the object of several studies (brain natriuretic peptide-guided fluid management [48, 49], vasodilators [50, 51], inotropic drugs [52]).

In recent years, diaphragmatic dysfunction has emerged as a likely determinant of difficult weaning from MV [13, 53], and observational data have suggested that the recovery of inspiratory muscle force could favor weaning success [54]. This leads to the idea that restoring diaphragm strength could be clinically useful. Results of small studies suggest that diaphragm strength—a physiological outcome—can be improved in patients who are difficult to wean (with theophylline [55] or with inspiratory muscle training [56]). Beyond that, preliminary data indicate that inspiratory muscle training can facilitate weaning from MV [17], although heterogeneous results imply caution [16, 57, 58].

In this context, RESCUE 2 will test a technology that is completely novel and that will be used therapeutically for the first time. A major advantage of this approach is that, contrary to inspiratory muscle training, it does not require patient cooperation or motivation. The study will be larger in size than most of the studies that have previously attempted to demonstrate a benefit of a therapeutic approach in difficult-to-wean ICU patients. Because of the “first-of-its-kind” nature of the therapy, it was not possible to power the study according to previous data and a sample of convenience was chosen, which does constitute a methodological limitation. However, note that many published studies validating indicators predictive of weaning success or failure have been conducted in smaller or similar samples [34, 59, 60]. This suggests that a sample of this size should be sufficient to detect differences between success and failure among patients.

### Strengths, limitations, and uncertainties

#### Masking

A sham design has not been retained for the RESCUE 2 study because of the risks inherent to central venous catheterization. Therefore, the RESCUE 2 protocol does not require the placement of a central line in a control patient if this is not decided by the clinicians in charge of this patient in the context of routine care. The study is therefore controlled but not blinded, with the ensuing requirement for caution when interpreting the data. To limit the corresponding risk of bias, precautions have been taken to minimize the risk of discrepancies between the treatment and the control groups, notably regarding the inclusion process (e.g., requirement for a standardized VLT before inclusion in the study). Also, ultrasound diaphragm measurements will be evaluated by blinded operators at a core laboratory, which will allow one to credibly assess the ability of TTVDP to restore diaphragmatic mass and contractility in the study population, irrespective of the main outcome. Of note, blinded trials of medical devices are the exception rather than the rule.

#### Phrenic stimulation regimen

In the absence of an animal model relevant to difficult weaning from MV in humans, it was not possible to determine the optimal phrenic stimulation regimen in preclinical studies. The chosen regimen therefore derives from training protocols used in rehabilitation, such as the inspiratory muscle training study conducted by Martin et al. [17]. Of note, in RESCUE 2 phrenic stimulation is delivered with 200–300 μs pulses at 15 Hz, which is in the range of the parameters used to successfully mitigate VIDD in animal studies [22, 23] and known to provoke fused diaphragmatic contractions in humans [27].

#### Transposability of diaphragm pacing data in quadriplegics

The experience gained worldwide since the 1970s with diaphragm pacing attests to its efficiency at reconditioning the atrophied diaphragm in humans [21]. Diaphragm pacing-induced reconditioning in this context is sufficient to provide full breathing autonomy [21]. Success has been observed after years of disuse, namely in patients with extremely atrophic diaphragms. Yet ICU-acquired diaphragmatic dysfunction does not stem from disuse only, but most probably from an array of physiologic aggressions of various natures, including sepsis [61]. This could interfere with the anabolic effects of diaphragm pacing in a manner that is difficult to predict. In this regard, it is important to note that phrenic stimulation in patients who are difficult to wean from MV is not intended to provide full ventilatory support as in the case of quadriplegic patients, but only serves a reconditioning purpose. With this in mind, the ability of diaphragm pacing to mitigate “pure” VIDD in a preventive manner [22, 23] is reassuring.

